**Section 2 (strategies for supporting the change)**				
	**1. Doing cannabis-free activities**			
		Read about suggested distraction strategies Decide on and plan to engage in 2 cannabis-free activities	Behavior substitution Prompt goal setting Prompt behavioral practice Behavioral activation	
	**2. Getting social support**			
		Read about the importance of having an adequate support system Identify supportive persons	Provide information on social support (general and emotional) Prompt goal setting (social support) Prompt behavioral practice Behavioral activation	
	**3. Taking care of yourself**			
		Rank psychological and activity domains affected by cannabis use and psychosis Read information to promote a healthy lifestyle (eg, diet and sleep) Select a lifestyle modification goal and make a plan	Provide information Prompt intention formation Prompt goal setting Action planning Behavioral activation	
	**4. Managing your stress**			
		Identify stress symptoms Read about false stress triggers Read about stress coping strategies	Provide information Cognitive restructuring Monitoring with awareness Prompt behavioral practice Provide contingent rewards (badge, upon completion of 4 strategies) Behavioral activation	
	**5. Finding solutions to your problems**			
		Read about problem-solving steps Participate in exercises that incorporate problem-solving techniques	Provide information Skills training focused on problem-solving Behavioral activation	
	**6. Communicating effectively**			
		Read about verbal and nonverbal communication techniques Identify used communication techniques	Provide information Monitoring with awareness Skills training focused on problem-solving Behavioral activation	
	**7. Being assertive**			
		Read about communication modalities Participate in exercises that exemplify the use of assertive communication	Skills training focused on verbal and nonverbal communication Self-affirmation Behavioral activation	
	**8. Valuing and rewarding yourself**			
		Identify positive behavioral changes Select preferred encouragements Choose rewarding activities	Self-reward Anticipation of future rewards Prompt goal setting (activities) Provide contingent rewards (badge, upon completion of 8 strategies) Behavioral activation	
	**9. My journey**			
		Self-assessment of reaching cannabis use and personal goals Identify useful strategies and behaviors Provide plans for future projects Access web-based resources about cannabis and psychosis	Provide feedback on outcomes and behavior Prompt goal setting (activities) Monitoring with awareness or relapse prevention Provide general encouragement Provide contingent rewards (badge)	

^a^Corresponding to the taxonomy of behavior change techniques published by Abraham and Michie [49] and Michie et al [50].

**Table 3 table3:** Activities and behavioral change techniques for follow-up modules (boosters).

Module and activities				Behavioral change techniques^a^
**Follow-up modules (boosters)**				
	**Booster 1**			
		Read a personalized report about reasons or motivations for behavioral change, cannabis dependence, and goals Self-assess their progress toward goal achievement Read a personalized report about psychological strengths, triggers, withdrawal cravings, and stress symptoms Identify useful strategies Identify reasons for not reaching their goal (if applicable) and receive tailored solutions	Review of behavioral and outcome goals Provide feedback on outcomes and behavior Monitoring with awareness or relapse prevention Provide general encouragement Prompt goal setting (for those who did not reach their goals) Prompt behavioral practice	
	**Booster 2**			
		Reassess their severity of dependence Set a cannabis use goal for the next month Update preferred strategies	Same as for booster 1	
	**Booster 3**			
		Report on positive changes and successful strategies (abstinent) Complete questionnaires related to influence of cannabis on psychotic symptoms; cannabis use consequences (nonabstinent) Self-report of social functioning, symptoms, and useful strategies (nonabstinent)	Same as for booster 1	

^a^Corresponding to the taxonomy of behavior change techniques published by Abraham and Michie [49] and Michie et al [50].

#### EIS Characteristics

Participants in the control group will receive EIS for psychosis through an interdisciplinary approach offered by teams of clinicians, including physicians and case managers with various backgrounds (eg, nurses, occupational therapists, and social workers), and interact with clinicians as per standard EIS procedures, which commonly include weekly case manager visits and follow-up visits with physicians every 3 weeks. At EIS clinics, individuals with FEP will receive intensive treatment (typically for 3 years) with the possibility of extension based on case-by-case evaluation. Services offered will comprise medication management; psychiatrist and case manager follow-up; and a range of psychosocial interventions including psychoeducation, psychotherapy (eg, CBT for psychosis), family interventions, peer support, interventions for substance use disorder (including CUD; ie, psychosocial interventions such as MI, CBT, psychoeducation, and harm reduction), support for basic life needs (eg, food and shelter), and support for improving social functioning (eg, employment and education). The receipt of interventions or services for cannabis use will be documented in the Intervention and Services Form at weeks 6, 12, and 24 assessments.

#### Modified EIS

Participants in the intervention arm will receive all services included in EIS, with the exception of concomitant formal psychological interventions for treating CUD, such as MI or CBT individual or group therapy sessions. Clinicians will be assigned an active supporting role, as our formative research showed that participants would like to receive support from clinicians for completing app modules or feedback related to their progress in the intervention at a frequency of approximately once per week. This implies asking about any difficulties with iCC and offering support with the content during each clinical encounter, as requested by the participants. Clinicians will use personalized login credentials to access the iCC dashboard and monitor the progress of the participants in the intervention (eg, number of modules completed and frequency) if allowed by the participant to do so.

### Measurements

#### Schedule, Sociodemographic Data, and Social Support

Clinical research assistants will conduct all assessments at baseline and at weeks 6, 12, and 24 after consent, in person, over the phone, or using telemedicine. Data will be stored in REDCap (Research Electronic Data Capture), a secure, web-based software platform designed to support data capture for research studies [53,54] (see Figure 2 for assessment and procedure schedule corresponding to the Standard Protocol Items: Recommendations for Interventional Trials [SPIRIT] statement [55]). Sociodemographic data will be collected at baseline and will include gender identity, biological sex, ethnicity, educational attainment, employment or studying status, income, living arrangements status, and housing status. To measure social support, we will use the 10-item Social Provisions Scale, which has been validated in individuals with schizophrenia and includes 5 domains: tangible help, emotional support or attachment, orientation, reassurance of worth, and social integration [56]. Items will be measured on a 4-point Likert scale from “1-totally disagree” to “4-totally agree,” and higher total scores (range 10-40) indicate better social support.

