## Methods

### Study Design

This study is a two-arm, parallel group (1:1 ratio) pilot RCT of iCC for decreasing cannabis use and modified Early Intervention Services for psychosis (mEIS) compared with EIS for young adults with FEP. Study participation may last up to 28 weeks and include a 14-day screening period (with an additional 14-day window to complete the baseline assessments), a 12-week intervention period, and a 12-week booster session and follow-up period (Figure 1). The CONSORT-EHEALTH (Consolidated Standards of Reporting Trials of Electronic and Mobile Health Applications and Online Telehealth) [43] guidelines were used to describe the protocol.

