### Recruitment

The study will be conducted at 6 participating clinics that provide EIS for psychosis (ie, 5 sites in the province of Quebec and 1 in Nova Scotia), and additional sites may be added as needed over the course of the study to maximize recruitment.

Potential participants will be identified by the clinical staff who will document on the screening form the general eligibility and exclusion criteria and obtain permission from the participants to be contacted for research purposes. The research assistant will contact potential participants in person at the clinic or using an internet-based communication platform.

Once informed consent is obtained, the research staff will conclude the eligibility assessment by documenting on the screening form the eligibility and exclusion criteria reserved for the research staff. The enrollment process will conclude with the collection of participant contact information using the locator form.

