### Randomization and Blinding

Once baseline assessments are completed, participants will be randomized to either (1) iCC+mEIS or (2) EIS. Within each stratum, based on biological sex, a random 1:1 group allocation sequence is generated using a permuted block design with blocks of varying sizes to decrease the likelihood of predictability of group assignment. The group allocation will not be masked, and the baseline visit concludes with participants logging into iCC and completing the introductory module. If a participant drops out of the study at any point following randomization, the randomization slot will not be reallocated to a new participant. The randomization schedule is concealed within the secure REDCap system and was created by the CHUM Center for the Integration and Analysis of Medical Data (CITADEL). The study participants, clinicians, and research staff conducting assessments will not be blinded to the group assignment, while individuals performing analyses will be blinded.

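### The visit schedule counts weeks 6, 12 and 24 from consent, which contradicts the protocol's own 28-week timeline and leaves the week-12 time point 8 to 12 weeks after randomisation

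*Protocol article*

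**What the plan says.** All references are to the Protocol article.

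- **Visit clock.** Schedule, Sociodemographic Data, and Social Support: "Clinical research assistants will conduct all assessments at baseline and at weeks 6, 12, and 24 after consent".
- **Overall timeline.** Study Design: "Study participation may last up to 28 weeks and include a 14-day screening period", "with an additional 14-day window to complete the baseline assessments", then "a 12-week intervention period, and a 12-week booster session and follow-up period".
- **Order of events.** Recruitment: "Once informed consent is obtained, the research staff will conclude the eligibility assessment". Randomization and Blinding: "Once baseline assessments are completed, participants will be randomized to either (1) iCC+mEIS or (2) EIS". In the iCC arm the baseline visit ends with app login and module 1.
- **Meaning of week 12.** Statistical Analyses labels the 12-week cannabis-quantity analysis as end of intervention. Study Strengths and Challenges ties week 12 to the end of the main iCC programme.
- **App data.** Secondary Outcomes provides for automatic collection over 24 weeks of participation in the intervention.
- **What is read at week 12.** Under the primary outcomes, retention means completing all week-12 assessments, and control-arm engagement is taken at that assessment. iCC completion requires the ten section 1 modules plus at least one follow-up module on the participant's cannabis goal, with the information drawn from the app.

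**The concern.** Consent comes before eligibility is finalised, before baseline and before randomisation. A visit counted from consent is therefore not the same visit as one counted from the start of the intervention. The schedule section uses the first origin; the overall timeline and the meaning given to week 12 require the second.

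This matters because week 12 carries both primary outcomes and the main cannabis-use comparison. iCC completion and retention are each judged against an absolute 50% threshold, so a time point that drifts with screening speed cannot be relied on to cancel out between arms. A site that follows the schedule sentence would also book visits on different dates from a site that follows Study Design.

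**Working it through.** **1. Reproduce the plan's own total.** Study Design gives 14 days screening, 14 days extra for baseline, 12 weeks of intervention and 12 weeks of follow-up:

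2 + 2 + 12 + 12 = 28 weeks, as stated.

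This works only if the two 12-week periods begin after screening and baseline. If week 24 is counted from consent, the last visit is 24 weeks after consent, 4 weeks short of the 28-week maximum.

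**2. Is a gap between consent and randomisation built in?** Yes. Beyond the order of events above, Study Consent, Compensation, and Data Security pays CAD $30 per attendance up to CAD $150. 150 / 30 = 5 payments: screening, baseline, and weeks 6, 12 and 24. Screening and baseline are thus paid separately.

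**3. Time since randomisation at each visit, if weeks are counted from consent.** Time since randomisation = visit week − gap, with the gap between 0 and 4 weeks (28 days).

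| Gap (weeks) | Week-6 visit | Week-12 visit | Week-24 visit |
|---|---|---|---|
| 0 | 6 | 12 | 24 |
| 1 | 5 | 11 | 23 |
| 2 | 4 | 10 | 22 |
| 3 | 3 | 9 | 21 |
| 4 | 2 | 8 | 20 |

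At the 4-week extreme, the 14-day Timeline Follow Back at the week-12 visit would cover weeks 6 to 8 after randomisation instead of weeks 10 to 12.

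**4. Effect on iCC completion, if the app count were also stopped at the week-12 visit.** Inputs: module 1 is done at baseline, which leaves 9 modules to reach module 10. The goal-review module, read here as the follow-up module in the completion definition, is offered two weeks after module 10 (Development and Content). The slowest qualifying pace is 9 / (weeks available − 2):

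- 12 weeks available: 9 / 10 = 0.9 modules per week.
- 8 weeks available: 9 / 6 = 1.5 modules per week.

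At the recommended 2 per week, module 10 is reached at 9 / 2 = 4.5 weeks (5 weeks if module 1 is counted too), and the follow-up module opens at 6.5 to 7 weeks. The definition can therefore be met even within 8 weeks. Only participants working at about 0.9 to 1.5 modules per week would change status at the extreme gap, and the band is narrower for shorter gaps.

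**5. Sample size.** The stated 33 per arm reproduces as (1.645 + 0.842)² × 0.7 × 0.3 / 0.2² = 32.5, rounded up to 33. No term depends on the visit origin, so it is unchanged.

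**The case against.** The strongest reply is that one loose phrase is being read against a protocol that otherwise points clearly to an intervention clock. Study Design, Secondary Outcomes, Statistical Analyses and the Discussion all do so. The schedule section refers to Figure 2, which is not reproduced in the text at hand and may show the intended origin. This lowers confidence that visits would really be held early. It does not remove the contradiction, because the schedule sentence is the only visible text that states the visit origin, and the origin it states does not fit the rest.

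A reader might also infer three stronger things, which the document does not support:

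- **That the primary completion rate is cut short.** Module completion is logged automatically for 24 weeks. Statistical Analyses says only that it is judged at week 12, and nothing says that the count stops on the visit date.
- **That 8 weeks is the typical exposure.** It needs both 14-day windows to be used in full after consent. Clinic staff fill in part of the screening form before consent, Study Design does not say that the screening period starts at consent, and no expected gap is given.
- **That the programme cannot fit.** All 21 modules would take 21 / 2 = 10.5 weeks at the recommended pace, but faster progress is permitted and completion does not require all 21.

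Finally, any gap arises before allocation, so it is balanced between arms in expectation and does not bias the cannabis-quantity comparison.

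**Conclusion.** The point stands as an internal contradiction in a stated rule. Counted from consent, the week-12 visit falls 8 to 12 weeks after randomisation, and 8 is the extreme. Retention, control-arm engagement and the 14-day cannabis quantity would be read at that variable time. The cannabis comparison would remain fair between arms but would reflect a shorter exposure for some participants than its end-of-intervention label implies.

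An understated iCC completion rate is conditional. It requires the app count to be cut at the same visit, and it then affects only participants at roughly 0.9 to 1.5 modules per week. The document gives neither a distribution of pace nor one of the gap, so no figure can be put on the loss. The result rests on two readings: that the gap can use the whole 28 days after consent, and that the follow-up module in the completion definition is the one released two weeks after module 10.

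**What to change.** In the schedule section, state that assessments are at weeks 6, 12 and 24 after randomisation. Define day 0 as randomisation, so that the schedule agrees with the 28-week timeline in Study Design, and check that Figure 2 uses the same origin. In the primary outcome definition, state that iCC completion is counted from app logs through day 84 after randomisation (12 × 7 = 84), whatever the date of the visit.

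The cost is wording, the visit dates set in REDCap and a note to site staff. There are no extra visits and no change to the sample size. Because the app logs run for 24 weeks, completion can be counted this way for participants already enrolled as well.

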**Figure 2 figure2:**
[figure not shown]
Schedule of enrollment, allocation, interventions, and assessments. W: week.

#### Primary Outcomes: Intervention Completion and Trial Retention Rates

For both outcomes, the denominator will represent the total number of participants randomized to the intervention or control groups. For iCC intervention completion, the numerator represents the number of participants who completed all 10 modules of the first section and at least 1 follow-up module related to involvement in reaching their cannabis use objective. This information will be collected through iCC. For participants randomized to the control group, the numerator will represent the total number of those who participated in EIS and ongoing engagement with EIS at the time of the 12-week assessment. The ongoing engagement with EIS will be documented using data collected through the Intervention and Services Form related to the receipt of services for cannabis use (at all study visits) and data from medical health records pertaining to receipt of any interventions that are offered at the clinic. For retention rate in both study groups, the numerator will be the number of participants who completed all week 12 (end point) assessments.

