**Methods:**

Consenting individuals (n=100) meeting the inclusion criteria (eg, aged 18-35 years with FEP and CUD) will be randomly allocated in a 1:1 ratio to the intervention (iCC+modified EIS) or control (EIS) group. The iCC is fully automatized and contains 21 modules that are completed over a 12-week period and 3 booster modules available during the 3-month follow-up period. Validated self-report measures will be taken via in-person assessments at baseline and at 6, 12 (end point), and 24 weeks (end of trial); iCC use data will be collected directly from the mobile app. Primary outcomes are intervention completion and trial retention rates, and secondary outcomes are cannabis use quantity, participant satisfaction, app use, and trial recruiting parameters. Exploratory outcomes include severity of psychotic symptoms and CUD severity. For primary outcomes, we will use the chi-square test using data collected at week 12. We will consider participation in iCC acceptable if ≥50% of the participants complete at least 11 out of 21 intervention modules and the trial feasible if attrition does not reach 50%. We will use analysis of covariance and mixed-effects models for secondary outcomes and generalized estimating equation multivariable analyses for exploratory outcomes.

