	**Supplementary module: return to objective**			
		Follow-up on their objective defined in module 10. This module can be offered for a maximum of 2 times once participants start section 2.	Prompt barrier identification Relapse prevention Provide general encouragement Prompt review of behavioral goals	

^a^Corresponding to the taxonomy of behavior change techniques published by Abraham and Michie [49] and Michie et al [50].

^b^CUD: cannabis use disorder.

^c^MI: motivational interviewing.

The app is fully automatized and contains 2 sections and 3 booster modules. The first section contains 10 modules that are completed sequentially at a recommended frequency of 2 per week; however, faster progress will be permitted upon reading a prompt related to the recommended frequency. Two weeks after module 10, in which participants will self-identify a cannabis use goal, an additional module (that can be repeated after 2 weeks) will be offered to facilitate consolidating and reviewing participant goals (Table 1). Section 2 will unlock after section 1 is completed and consists of 8 modules (focusing on coping skills strategies) that can be completed in the preferred order while respecting the recommended frequency and concludes with a recapitulative module (Table 2). During the 3-month follow-up, participants will complete 1 booster session per month (which includes a summary of the content provided in the first 2 sections) to promote long-term behavioral changes (Table 3).

A summary of personalized responses provided in each module will be saved and can be accessed by the participant through the app dashboard. Additional dashboard features will include an information tab that provides links to relevant web-based resources related to psychosis and cannabis consumption; a “Profile” tab where the participant can rapidly access the most relevant information provided during module completion; a “Settings” tab where they will select their preferred language (English or French) and notification preferences; and an emergency button that will allow them to contact their case manager (see Multimedia Appendix 3 for the relevant screenshots).

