### Statistical Analyses

The 1-sided chi-square 95% CI will be calculated to estimate the lower bound of iCC completion and trial retention rates. We will consider participation in iCC acceptable if more than 50% of the participants completed at least 11 out of 21 intervention modules at week 12. The trial will be considered feasible if the attrition at week 12 does not reach 50%. An analysis of covariance model will be used to provide a preliminary assessment of the effect of treatment on the quantity of cannabis use (dependent variable) at 12 weeks (end of intervention). The independent variables will be the quantity of cannabis use at baseline and a dichotomous variable reflecting arm allocation. The second model will include covariates that were found to be different between the groups at baseline. For participants’ satisfaction with the intervention, we will calculate the CSQ total scores as well as the mean and SD. The groups will be compared using a mixed-effects model with random intercepts for each site. For app use and trial parameters, we will use univariate analyses and report the distribution (frequency tables), central tendency (mean, median, and mode), and dispersion (range and SD).

For exploratory outcomes, we will compute descriptive statistics and bivariate and multivariable analyses using generalized estimating equation (GEE) models. The generalized estimating equation is a repeated-measures regression model that accounts for the correlations between repeated measures for each person [70]. We will use different types of GEE modeling depending on the distribution of the outcome. For cannabis frequency (count data), we will use Poisson; for the abstinence (binary), we will use binomial; and for continuous variables (ie, scores calculated for MPS, SDS, DTCQ, PANSS, PBSM, SWL, and SPS), we will use linear GEE modeling. Using this analytic approach, we will estimate the multivariable associations between the outcomes and study visits (ie, baseline and end of intervention), study condition (the reference group will be the control arm), and their interaction, as well as other predictors and covariates, such as sociodemographics, social support, CUD severity, behavioral stage of change, medication status, and other substance use. We will use the chi-square test of proportions to compare behavioral stages at different time points and between the 2 study arms.

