To consider the trial feasible, at least 50% of participants must complete all study assessments at week 12, which corresponds to the end of the iCC main intervention (excluding booster sessions). In the absence of similar trials in our target population, we chose this cutoff conservatively, as it is close to the maximum attrition rate of 65% reported in studies using app-based interventions for decreasing cannabis use in individuals *without psychosis* [34-36]. Our approach is justified by the clinical characteristics of participants attributable to psychosis and CUD, which could represent a barrier in complying with the study procedures. However, we expect an attrition rate closer to 30% because we tailored the iCC intervention to participants’ needs, restricted inclusion criteria to participants interested in using an app-based psychological intervention, and planned to offer iCC to participants allocated to the control arm at the end of the study. In addition, the intensive clinical follow-up that is offered in EIS for psychosis could contribute to lower attrition rates. Other implemented strategies that could reduce loss to follow-up include maintaining an updated record of participant contact information throughout the study, scheduling study visits according to participant availability, and offering flexible in-person or web-based study visit assessments.

In individuals with psychosis, face-to-face psychological interventions were found to be more effective in decreasing the quantity than frequency of cannabis used [22]. However, no study has evaluated the effects of mHealth interventions on the quantity of cannabis used in individuals with CUD and psychosis. In their RCT that included a web-based psychological intervention in individuals without psychosis, Rooke et al [35]) found a small effect (Cohen *d*=0.19) of a short 6-module intervention on the quantity of cannabis consumed at the 12-week follow-up [35]. Similar to the intervention used by Rooke et al [35], iCC incorporates behavioral and motivational approaches tested by Copeland et al [47]. Our pilot study will offer valuable information related to using a higher-intensity 19-module intervention and offering support during clinical encounters to participants who have difficulties in completing iCC.

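### The primary iCC completion outcome has two nested numerators, so the same app data can give two different completion rates

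*Protocol article*

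**What the plan says.** All places are in the Protocol article.

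- **Primary Outcomes section.** For the iCC arm, "the numerator represents the number of participants who completed all 10 modules of the first section and at least 1 follow-up module", and that last module must concern the participant's cannabis use objective. The denominator is everyone randomized to the arm.
- **Statistical Analyses.** Participation is "acceptable if more than 50% of the participants completed at least 11 out of 21 intervention modules at week 12". The same paragraph plans a one-sided 95% interval to give the lower bound of the completion rate. The Abstract and Sample Size sections also use 11 of 21. Sample Size excludes the three boosters and attaches the expected 70% to this rule.
- **Development and Content.** Section 1 has 10 modules taken in sequence, and Section 2 opens only once they are done. Section 2 has 8 modules and a closing recapitulative one. The supplementary module is timed as follows: "Two weeks after module 10, in which participants will self-identify a cannabis use goal, an additional module" is offered, repeatable after another two weeks. Table 1 describes it as following up the goal set in module 10 and caps it at two offers.
- **Discussion.** The study is described as "using a higher-intensity 19-module intervention", against 21 modules elsewhere.
- **Control arm.** "For participants randomized to the control group, the numerator will represent the total number of those who participated in EIS and ongoing engagement with EIS". This is assessed at week 12.

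**The concern.** The section that defines the primary outcome and the sections that size and judge it do not count the same participants. The Primary Outcomes rule needs one particular module after Section 1. The 11-of-21 rule accepts any module after Section 1. Someone who finishes all 19 Section 1 and Section 2 modules but never opens the supplementary one has done 19 of 21, yet is not a completer under the Primary Outcomes wording.

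The acceptability decision rests on this rate. Group allocation is open and the app logs hold both counts, so the choice of numerator should not remain open once data can be seen. The planning rate of 70%, and hence the stated power, applies only to the broader rule.

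The control arm is also given a completion numerator, but it measures continued service engagement. Entry already requires active follow-up at an early psychosis clinic. It is a different construct from finishing app modules, although it sits under the same primary outcome.

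**Working it through.** **1. The plan's own sample size.** Inputs from Sample Size: null 0.50, expected 0.70, one-sided 5%, 80% power, binomial standard error with normal approximation.

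n = (1.645 + 0.842)² × 0.70 × 0.30 / (0.70 − 0.50)² = 32.46, so 33 per arm. Then 2 × 33 / 0.7 = 94.3. Both match the article (33; 94, rounded to about 100). This is a one-sample calculation against a fixed 50%.

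**2. Module count.** Section 1 has 10 modules and Section 2 has 8 + 1 = 9, which makes 19 distinct modules. Two offers of the supplementary module give 19 + 2 = 21. The article does not spell this sum out, but it reconciles the two totals.

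**3. How the two rules relate.** Call the Primary Outcomes rule A and the 11-of-21 rule B. Neither Section 2 nor the supplementary module is available before module 10 is done.

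- Reachable states: 10 with Section 1 unfinished (0 to 9 modules), plus 3 × 10 = 30 with Section 1 finished (0 to 2 supplementary, 0 to 9 Section 2). Total 40.
- B is met in 30 − 1 = 29 states (Section 1 plus at least one more module).
- A is met in 2 × 10 = 20 states (at least one supplementary completion).
- B without A: 29 − 20 = 9 states, namely Section 1 plus 1 to 9 Section 2 modules with no supplementary module. A without B: none.

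So A is nested in B.

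**4. Timing.** The supplementary module comes two weeks after module 10. A participant who finishes module 10 after week 10 cannot meet A by week 12, but meets B with a single Section 2 module. At the recommended two modules a week, module 10 falls at about week 5 and the supplementary module at about week 7, so this route concerns slow starters.

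**5. Pass mark with 50 in the iCC arm (100 randomized 1:1).** Lower bound = p − 1.645 × √(p(1 − p)/50).

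- 30/50: 0.60 − 0.114 = 0.486, fails.
- 31/50: 0.62 − 0.113 = 0.507, passes.
- Exact binomial at 0.50: P(X ≥ 31) = 0.059 and P(X ≥ 32) = 0.032, so 32 are needed.
- Plain cut-off of more than 50%: 26 are enough.

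**6. Effect on the decision.** Assume that 70% meet B and that a share q of those lack the supplementary module. The rate under A is then 0.70 × (1 − q). The documents give no q, so a range is shown.

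| q | Rate under A | P(≥31), normal approx. | P(≥32), exact | P(≥26), plain cut-off |
|---|---|---|---|---|
| 0 | 0.70 | 0.92 | 0.86 | 0.998 |
| 10% | 0.63 | 0.62 | 0.51 | 0.96 |
| 20% | 0.56 | 0.24 | 0.16 | 0.76 |
| 30% | 0.49 | 0.04 | 0.02 | 0.39 |

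**7. One data set, two results.** Suppose 33 of 50 meet B and 4 of them never did the supplementary module. B gives 33/50 (66%), which passes the lower bound. A gives 29/50 (58%), with lower bound 0.58 − 0.115 = 0.465, which fails. Both pass the plain cut-off.

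**The case against.** The strongest defence is that the rules nearly coincide. Gating makes 11 of 21 equal to Section 1 plus one more module, and the Primary Outcomes wording is also 10 + 1 = 11. At the recommended pace the supplementary module arrives well before week 12, and nothing in the article says many participants would skip it. This stands as a limit on size: the rules are nested, not incompatible, and if q is near zero they give the same answer.

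A second defence is that the written criterion is more than 50%, under which 58% or 60% still passes. That also stands in part. Statistical Analyses gives both a lower bound and a cut-off without saying which one is compared with 50%, so the size depends on the reading.

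A reader might go further and infer that completion will be tested between arms, with iCC bound to look worse than EIS engagement. The Abstract says "For primary outcomes, we will use the chi-square test using data collected at week 12" but names no contrast. Statistical Analyses plans a one-sided bound for the rates, and 33 per arm reproduces only as a one-sample calculation; a one-sided comparison of 0.50 with 0.70 would need 74 per arm. The documents do not state a between-arm test of completion.

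Two smaller points carry little weight. Table 3 uses the follow-up label for boosters, but Sample Size excludes boosters from the count and Table 1 points to the supplementary module. The figure of 19 modules is a Discussion remark that feeds no analysis.

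**Conclusion.** The point holds as a contradiction within the article about its own primary outcome. Two numerators are stated, the Primary Outcomes one is strictly narrower, and the 70% expectation belongs only to the broader one.

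If the lower bound decides, the chance of passing under the narrower rule falls from 0.92 to 0.62 at q = 10% and to 0.24 at q = 20%. This assumes 50 in the iCC arm, a true 11-of-21 rate of 70% and the normal approximation. If the plain cut-off decides, the corresponding figures are 0.998, 0.96 and 0.76. The values of q are assumptions, and the actual share is unknown.

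The control-arm numerator is a different construct and should not share the name. It does not show that an invalid between-arm test is planned.

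**What to change.** - Use one week-12 numerator in the Abstract, Primary Outcomes, Sample Size and Statistical Analyses sections. Harmonizing in either direction removes the contradiction. The better choice is the rule that the sample size and decision criterion already use: all 10 Section 1 modules plus at least one further non-booster module, from Section 2 or supplementary. The 33 per arm then stands unchanged.
- Report the version that requires the supplementary module as a supportive result from the same app logs.
- State that 21 means 19 distinct modules plus up to two offers of the supplementary module, and name that module wherever it is meant.
- Say whether the lower bound or the observed rate is compared with 50%.
- Report control-arm EIS engagement descriptively, as a separate measure and not as intervention completion.

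The cost is wording in the protocol and analysis plan. No new data are needed, and the sample size does not change if the 11-of-21 rule is kept. If the narrower rule is chosen instead, the 70% expectation has to be justified for it.
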